## Randomization

Due to the practical constraints of primary care settings, where it is challenging to manage test group and control groups separately within the same institution, cluster randomization will be used. Institutions will be randomized as either the test group [institutions managing subjects with the 'Well Check' app in conjunction with the investigator (responsible physician)] or the control group (institutions where subjects use the 'Well Check' app for self-management).

For cluster randomization, participating primary medical institutions will be divided into small groups based on basic characteristics [age of the treating physician (45 years and older, or younger), region (metropolitan, non-metropolitan)]. Within these small groups, the test group and control group will be randomly assigned in a 1:1 ratio using the cluster randomization method.

To ensure strict randomization, an independent person not related to this clinical study will prepare the randomization list using the Proc PLAN procedure of SAS (Ver. 9.4 or higher, SAS Institute, Cary, NC, USA). The generated randomization list will be provided to the IWRS (interactive web response system) developer. The randomization number will be verified through IWRS.

After obtaining written consent for participation in this clinical study, the subject's screening test results will be evaluated. Only those who meet the inclusion criteria and do not fall under the exclusion criteria will be assigned a Randomization Enrollment Number.

The randomization enrollment number will be given out as “AAA-RXX-YYY” and means the following.

- “AAA”: Institution identification number
- “R”: Cluster Randomization
- “XX”: Stratification identifiers [age of the treating physician (45 years and older, or younger), region (metropolitan, non-metropolitan)]

- “YYY”: Order of randomly assigned subjects

|  | Metropolitan (X1) | Non-metropolitan (X2) |
| --- | --- | --- |
| 45 years and older (1X) | 11 | 12 |
| 45 years or younger (2X) | 21 | 22 |

# Investigational Software

## Information on the Investigational Software

**
[figure not shown]
**

The hospital-linked digital health application Well Check differentiates itself from other simple digital health applications by connecting the “Patient Application (App)” with the “Physician Web (Web) and Electronic Medical Record (EMR)” to manage diabetes and hypertension. Physicians can conveniently monitor patients' health statuses and manage them via the “Physician Web.”

Well Check allows users to record blood pressure, blood sugar, and specific health issues through surveys. If blood pressure and blood sugar are not recorded at least once a week, the application sends an alert to the user. The data is then transmitted to the physician for analysis and monitoring. If the recorded blood pressure or blood sugar levels are too high or low compared to the target, the physician can send feedback messages for management based on their judgment. This enables physicians to manage patients and monitor high-risk patients separately. Additionally, users can check how effectively their numbers are managed compared to the target in their preferred format—graphs, lists, or tables. Furthermore, the National Health Insurance Service links the results of health check-ups conducted throughout a patient's lifetime and provides them to the primary care physician, who can then send feedback messages to the patient.

1. **Key Features of the Well Check Application**
2. Integration with Hospital Charts (EMR) – Aegis, C-Chart, BeatA, Sense, WehagoH
3. Analysis of blood pressure, blood sugar, medication, concomitant symptoms, and lifestyle habits, etc.
4. Monitoring high-risk patients, with visit reminders when necessary
5. Sending messages from the primary care physician
6. Integration of health check-up results
7. Recommendations for tests and education
8. Analysis of continuous glucose reports
9. Support for overseas medical care services
10. Obesity management
11. **How to Use the Well Check Application**
12. Hospital Account Registration and Settings

- Initial registration (<https://www.well-check.co.kr>) 🡪 Access Physician Web 🡪 Set up hospital profile 🡪 Configure other hospital settings (treatment goals, monitoring criteria, test settings)

1. At the First Visit to Physician
2. Connect patient with hospital (Patient App – Physician Web link)
3. Assess patient's medical history and lifestyle habits
4. Recommend tests and provide education for diabetes management
5. Integration of health check-up results
6. Conduct basic surveys and laboratory tests
   During Each Visit -Review patient self-records and provide consultation
7. Understand patient symptoms and lifestyle
8. Blood Sugar Overview: Pre-meal/post-meal trends, estimated changes in HbA1c
9. Review blood sugar/blood pressure/medication records together: Patients using the medication reminder function
10. Analyze medication adherence
11. At Testing – Transmit test results within the hospital
12. Send individual test results and provide counseling
    - Input results from in-hospital measurements (blood sugar/HbA1c, blood lipids, liver function, body composition) into the Physician Web and send to patients, with cumulative management of past records
13. Calculate cardiovascular disease complication risk:
     Input cholesterol and blood pressure values
14. Review health check-up results
15. Post-Consultation Management
16. Provide diabetes education content (twice a week)
    - Cover disease information, dietary habits, exercise, and complication management
    - Track completion rates of educational content
17. Monitoring high-risk patients (weekly)

- Set management goals and alert criteria for blood sugar, blood pressure, and weight; monitor and manage weekly if targets are exceeded
- Utilize “Send Message” and “Teleconsultation” features

1. Monitor adherence to self-recording of blood sugar, blood pressure, and weight (weekly)

- Identify and encourage those who have not entered records, by sending encouragement messages (managed patients should enter self-records at least once a week, check for complications monthly)

## Use of Investigational Software

In this clinical study, the use of 'Well Check' by study subjects will be fully determined by the investigator (physician) based on the subject's medical condition, within the functional scope of the investigational software in a real-world clinical environment.

#

# Data Management

## Source Documents

Source documents are defined as records and materials resulting from data collection activities and observations in this study. They include, but are not limited to, the following clinical trial-related materials.

1. Source document data and records: Subject information sheets and consent forms, medical records, laboratory test records, records held by the pharmacy and laboratory departments involved in the clinical study, etc.
2. All original records or certified copies of original records containing clinical findings, observations, or other activities necessary for the replication or evaluation of the clinical study.

All source documents in this study will be recorded and stored by the investigators at the study site. Access to source documents will be restricted to authorized personnel only.

## Data Entry

The sponsor or delegated personnel will manage the data according to the Standard Operating Procedures (SOP). Monitors will ensure that the entries in the eCRF match the source documents and that the information is appropriate. They will take measures to prevent further collection or additional modifications of the eCRF. Data managers will check the appropriateness of the data entered in the eCRF and verify that it is correctly entered into the database, checking for any logical inconsistencies in the database.

Data for this study will be collected using a pre-designed eCRF. All Electronic Data Capture (EDC) systems used will comply with the Code of Federal Regulations (CFR) (21 CFR Part 11) and guidelines for processing and managing electronic data in clinical studies. The EDC system is an accredited electronic data collection system accessible only by authorized personnel. The system will record all traceable activities, including eCRF data entry, modification, storage, and deletion. The sponsor may request verification or correction of the collected data during the processing. The investigator is responsible for responding to these requests by rechecking or correcting the data and ensuring the data entered into the eCRF is accurate, complete, decipherable, and timely through electronic signatures. After the study concludes, copies of the eCRFs created through the EDC system will be stored on electronic media and provided to each study site. They will be archived under the same conditions as other essential documents.

## Data Verification

In case of discrepancies between the eCRF and source documents, inappropriate entries, or logical inconsistencies, the sponsor or data manager, along with the principal investigator, will review the validity of the concerned items. If necessary, corrections will be made and documented accordingly.

Once the sponsor verifies that there are no errors in the eCRF and the database, the database will be locked to prevent any unauthorized or accidental changes. Once locked, the clinical study data cannot be modified arbitrarily.

## Data Storage

The principal investigator is responsible for storing and managing all collected data and records (including electronic documents) at each site, including those from subjects who withdrew consent or dropped out.

All documents collected during the study must be stored in a secure, locked cabinet accessible only to the principal investigator, co-investigators, and delegated study personnel.

According to Article 15 of the Enforcement Rules of the Bioethics and Safety Act, the principal investigator must retain all documents for three years from the end date of the clinical study (However, the sponsor may extend the storage period if deemed necessary).

These documents are subject to audits by the sponsor or relevant regulatory authorities, and the investigator must not destroy any documents related to the clinical study without the sponsor's written consent. The investigator must seek preventive measures to avoid any accident or early destruction of such documents.

Upon the expiration of the retention period, paper documents will be shredded immediately, and electronic documents will be destroyed in a manner that prevents their recovery or restoration, as per the sponsor's agreement.

## Access to Data

Sponsor, monitor and auditor involved in this study may have access to the subject’s records for the purpose of monitoring and auditing the study and managing the progress. By entering into the study agreement, the investigator acknowledges that monitors and auditors from the sponsor and/or Contract Research Organization (CRO) may review the study subjects' charts and case report forms.

This information must be kept confidential and facilities with appropriate confidentiality standards and management protocols must be in place. The investigator must provide the necessary support to the sponsor and/or CRO. The investigator must also grant authorized representatives from the sponsor, regulatory authorities, and IRB direct access to the original medical records of the study subjects for the verification of study procedures and data.

# Evaluation Criteria and Methods, and Statistical Analysis Methods

## Endpoints

1. **Efficacy Endpoints**
2. **Primary Efficacy Endpoint**

- Percent change and change of HbA1c at 24 weeks compared to baseline

1. **Secondary Efficacy Endpoints**
   1. Percent change and change of FPG at 6, 12, 18, and 24 weeks compared to baseline
   2. Percent change and change in HbA1c at 6, 12, and 18 weeks compared to baseline
   3. Proportion of subjects achieving HbA1c < 7% at 6, 12, 18, and 24 weeks compared to baseline
   4. Proportion of subjects achieving HbA1c < 6.5% at 6, 12, 18, and 24 weeks compared to baseline
   5. Proportion of subjects achieving therapeutic response [change in HbA1c (baseline HbA1c – HbA1c at each evaluation time point) > 0.5% or HbA1c < 7%] at 12 and 24 weeks compared to baseline
   6. Change in blood pressure (systolic and diastolic) at 6, 12, 18, and 24 weeks compared to baseline
   7. Change in BMI and weight at 6, 12, 18, and 24 weeks compared to baseline
   8. Proportion of subjects with a reduction of 5% or more in weight and BMI at 6, 12, 18, and 24 weeks compared to baseline
2. **Exploratory Endpoints**
3. Change in lipid levels (total cholesterol, LDL-C, HDL-C, triglycerides) at 6, 12, 18, and 24 weeks compared to baseline
4. Change in liver function markers (AST, ALT, γ-GTP) at 6, 12, 18, and 24 weeks compared to baseline
5. Change in renal function markers (e-GFR, UACR, UGCR) at 6, 12, 18, and 24 weeks compared to baseline
6. Change in body composition analyzer indicators (skeletal muscle mass, body fat mass, body fat percentage, muscle mass, waist/hip circumference, body water, intracellular water, extracellular water, extracellular water ratio, abdominal fat percentage) at 12 and 24 weeks compared to baseline
7. Change in cardiovascular disease complication risk (ASCVD risk) at 12 and 24 weeks compared to baseline
8. **Safety Endpoints**
9. Laboratory tests, vital signs, physical examination results

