## Rationale

Based on the pilot study results, the difference in average HbA1c between the test group and the control group after 24 weeks of using Well Check in Type 2 Diabetes patients was considered to be 0.4% (8.0% vs. 7.6%), with a standard deviation (*s*) of 1.1%. Referring to these results, the total sample size (*n*) required was estimated to be approximately 274 subjects using G*Power 3.1.9.7.

Since this study employs cluster randomization, we further adjusted the sample size calculation by incorporating the design effect to account for potential intra-cluster correlations among patients within the same clinic. We calculated the design effect using the standard formula:

$$Design effect=1+\left( m-1 \right)\times ICC$$

Referring to previous studies conducted in primary care settings for patients with type 2 diabetes [11, 12], we conservatively adopted an intraclass correlation coefficient (ICC) value of 0.02 and assumed an average cluster size (*m*) of 20 participants per center. Therefore, we calculated the resulting design effect to be 1.38, and applying this adjustment to the initial sample size estimate gives a revised total sample size of 378 participants. Finally, considering an anticipated dropout rate of approximately 20%, we adjusted the target recruitment number further to approximately 480 participants.

[figure not shown]

< Calculation for Subject Number – Based on Glycated hemoglobin>

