## Inclusion Criteria

Select individuals who meet all of the following criteria:

1. Adults aged 19 to 80 years
2. Patients with Type 2 Diabetes who are currently receiving or are scheduled to receive Envlo Tab. or Envlomet SR Tab. based on the approved conditions
3. Individuals who have no difficulty using a digital healthcare smartphone application on their smartphone
4. Individuals who plan to engage in appropriate exercise and dietary therapy for blood glucose control during the clinical study period
5. Women of childbearing potential and men who agree to use appropriate contraceptive methods or have no plans for pregnancy during the observational study period

*Hormonal contraceptives, intrauterine device (IUD) or intrauterine system (IUS) implants, vasectomy, tubal ligation, double barrier methods (simultaneous use of cervical cap or diaphragm with male condom), etc.

1. Individuals who have listened to and understood the detailed explanation of the clinical study, and have voluntarily signed a written informed consent agreeing to participate in the study and to comply with subject precautions during the study period

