## Exclusion Criteria

Individuals who meet any of the following exclusion criteria will be excluded from this clinical study

1. Individuals with diabetes other than Type 2 Diabetes (e.g., Type 1 Diabetes, Diabetic Ketoacidosis, Gestational Diabetes, etc.)
2. Individuals who fall under the contraindications for administration according to the approved conditions of Envlo Tab. or Envlomet SR Tab.

- Patients who have hypersensitivity or a history of hypersensitivity to any component of Envlo Tab. or Envlomet SR Tab.
- Individuals with an estimated Glomerular Filtration Rate (eGFR) less than 30 mL/min/1.73m²
- Patients with renal impairment with an eGFR less than 60 mL/min/1.73m², end-stage renal disease, or those on dialysis
- Individuals with moderate to severe hepatic impairment (AST or ALT > 3 times the upper limit of normal, Total Bilirubin > 2 times the upper limit of normal, hepatitis, or liver failure)
- Individuals classified as class III or IV according to the New York Heart Association (NYHA) classification

1. Patients who have undergone treatment with obesity medications or weight loss drugs, or other treatments (surgery, diet, etc.) leading to unstable weight within 3 months prior to the enrollment date
2. Individuals with mental incapacity
3. Pregnant or breast-feeding women
4. Individuals participating in another clinical trial and receiving investigational drugs or investigational medical devices
5. Individuals who have prior experience using the Well Check application before study enrollment
6. Individuals deemed unsuitable for participation in this clinical study based on the judgment of the investigator (responsible physician)

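### The HbA1c target and therapeutic-response endpoints count patients already at target at baseline, including some whose HbA1c rises, and adjust for baseline HbA1c only conditionally

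*Protocol*

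**What the plan says.** Section 7.1, repeated in the synopsis and in 2.2, lists three secondary endpoints that classify a subject by HbA1c at the visit:

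- "Proportion of subjects achieving HbA1c < 7% at 6, 12, 18, and 24 weeks compared to baseline"
- "Proportion of subjects achieving HbA1c < 6.5% at 6, 12, 18, and 24 weeks compared to baseline"
- therapeutic response, defined as a fall in HbA1c from baseline of "> 0.5% or HbA1c < 7%] at 12 and 24 weeks compared to baseline"

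The two limbs of the third are joined by *or*, so an on-visit value below 7% is enough by itself.

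Section 3.3 admits "Patients with Type 2 Diabetes who are currently receiving or are scheduled to receive Envlo Tab. or Envlomet SR Tab", which includes patients already treated. Neither 3.3 nor 3.4 contains an HbA1c criterion. The efficacy analysis set in 7.2 requires a post-baseline HbA1c and sets no condition on the starting value.

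On adjustment, 7.2 (Demographic and Baseline Characteristics) names HbA1c among the variables to be checked, and makes a variable a covariate in later analyses if its standardized mean difference (SMD) exceeds 0.1. The paragraph on secondary endpoints calls for patient-level covariates without naming them.

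**The concern.** The stated objective is to confirm improvement. The words *achieving* and *therapeutic response* suggest that a patient moved to a better state, but the definitions do not require it. They combine three groups: patients who reached the target, patients who stayed there, and patients who lost ground but remained under the threshold. The phrase *compared to baseline* does not help, because the protocol never says what it means for a proportion at a threshold.

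Two things are at stake. First, the proportions will be read as attainment when part of them is maintenance or deterioration. Second, each arm's proportion depends on how many of its patients started at target. With 24 institutions randomized and patients consented and enrolled at institutions already assigned to an arm, that share could differ between arms without any effect of the app.

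**Working it through.** **What the rule does.** A patient going from 6.0% to 6.9% meets the 7% endpoint and counts as a therapeutic response. A patient going from 6.0% to 6.4% meets all three endpoints. Both have a higher HbA1c than at baseline.

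**Inputs.** The protocol states no figure for these endpoints and no baseline HbA1c distribution. Section 3.2 gives "8.0% vs. 7.6%), with a standard deviation" of 1.1%; the two means are 24-week values. I assume a normal baseline with SD 1.1 and use 7.6 and 8.0 as candidate baseline means. The sample size does not depend on this: 274 × 1.38 = 378, and 378 / 0.8 = 473 against a target of about 480, all for a difference in mean HbA1c.

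**Share already below threshold at baseline**, Φ((threshold − mean) / 1.1):

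| Baseline mean | Below 7% | Below 6.5% |
| --- | --- | --- |
| 7.6 | Φ(−0.545) = 29.3% (141 of 480) | Φ(−1.000) = 15.9% (76) |
| 8.0 | Φ(−0.909) = 18.2% (87 of 480) | Φ(−1.364) = 8.6% (41) |

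Widening the mean to 7.2 or 8.4 gives 42.8% or 10.2% below 7%.

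**Who the control responders are.** Simulation of 2 million patients: bivariate normal, SD 1.1 at both times, correlation 0.6, mean control change 0 or −0.3.

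| Baseline mean | Control change | Therapeutic responders already below 7% at baseline | Therapeutic responders whose HbA1c rose |
| --- | --- | --- | --- |
| 7.6 | 0 | 37% | 19% |
| 7.6 | −0.3 | 35% | 14% |
| 8.0 | 0 | 23% | 11% |
| 8.0 | −0.3 | 22% | 9% |

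With correlations of 0.5 to 0.7 and a mean change of 0 or −0.4, the ranges are 19% to 42% and 8% to 21%. In the correlation-0.6 setting, 42% to 57% of those below 7% at week 24 were already there at baseline.

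**How far an unadjusted baseline difference can distort the comparison.** An SMD of 0.1 is 0.1 × 1.1 = 0.11 points of HbA1c. With correlation 0.6, 0.6 × 0.11 = 0.066 points carry over to follow-up. With no treatment effect and no mean change, the proportions below 7% would then differ by:

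- mean 7.6: Φ((−0.6 + 0.033) / 1.1) − Φ((−0.6 − 0.033) / 1.1) ≈ 0.303 − 0.282, about 2 percentage points
- mean 8.0: Φ((−1.0 + 0.033) / 1.1) − Φ((−1.0 − 0.033) / 1.1) ≈ 0.190 − 0.174, about 1.6 percentage points

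For comparison, a true 0.4-point difference moves the proportion from 29.3% to 42.8% (mean 7.6) or from 18.2% to 29.3% (mean 8.0). Imbalance below the trigger is therefore a small disturbance beside the planned effect.

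**What always adjusting gains.** In a simulation that ignores clustering, adding baseline HbA1c to the model for HbA1c below 7% raised power from 81% to 89% (mean 7.6) and from 72% to 82% (mean 8.0). Restricting the analysis to patients at or above 7% at baseline went the other way: the test statistic fell from about 2.8 to 2.45 (mean 7.6).

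**The case against.** The other side has substantial points.

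- *The rule is identical in both arms.* This stands. A reader might infer that the endpoints bias the treatment comparison. The documents do not support that: the simulated shares describe the make-up of responders, and bias arises only if baseline control differs between arms.
- *Section 7.2 already deals with imbalance.* This stands in large part. HbA1c is a named baseline variable, and an SMD above 0.1 brings it into the models. What remains is that the adjustment is conditional, and the secondary-endpoint paragraph does not name baseline HbA1c. The synopsis lists only unadjusted tests, but that conflict with 7.2 is a separate matter.
- *The proportion at a guideline target is a coherent measure in an all-comers pragmatic trial, and the below-7% limb protects patients with little room to fall.* This also stands. A reader might infer that the endpoints must be restricted to patients above target, or that response should be the fall alone. Neither follows. Restriction changes the estimand and costs precision. Dropping the limb would count a patient stable at 6.3% as a failure.
- *Denominators and supportive tables can go in the statistical analysis plan.* That is true of the tables. The endpoint wording is in the protocol, in three places, and it labels some worsening patients as responders.
- *The size is unknown.* Agreed: every percentage here depends on an assumed baseline distribution.

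**Conclusion.** The point holds as one of interpretation and dilution. As written, three of the eight secondary endpoints credit patients who started at target, including some who worsened. If baseline HbA1c is roughly normal with SD 1.1, mean 7.6 to 8.0 and correlation 0.6 with week 24, about 18% to 29% of patients start below 7%, about 9% to 16% start below 6.5%, and about 9% to 19% of control therapeutic responders have a higher HbA1c than at baseline. Distortion between arms is possible but limited by the SMD rule; under the same assumptions, an imbalance just below the trigger moves the below-7% proportion by about 2 percentage points at most. The primary endpoint, its analysis and the sample size are untouched, and the continuous HbA1c analyses would still show mean worsening that these proportions can hide.

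**What to change.** 1. In 7.2, Secondary Efficacy Endpoints, include continuous baseline HbA1c as a fixed effect in every responder model, whatever its SMD.
2. In the synopsis, 2.2 and 7.1, keep the all-subject proportions but describe them as *at target* rather than *achieving*, and remove or define *compared to baseline* for them.
3. Report the proportions also by baseline status: *attained target* among subjects at or above the relevant threshold at baseline (7% or 6.5%), and *maintained target* among those below it. Show therapeutic response for the group with baseline HbA1c of 7% or more.

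No new data are needed, since baseline HbA1c is already collected. The cost is slightly more analysis and reporting, and smaller denominators in the supportive tables only: under the assumptions above, about 480 − 141 = 339 to 480 − 87 = 393 subjects at or above 7%, before dropout. If a logistic model is used, its adjusted odds ratio is conditional on baseline HbA1c, so the raw proportions by arm should be shown beside it.
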